### 4.4.2 Clinical determinants

For each reference cervical HPV infection with a given HPV type over the 48-month follow-period, the following determinants will be defined:

- HPV type: 16; 18; 31; 33; 45; Other high risk HPV type; Other low risk HPV type.

The above categorization of HPV types will be used in the univariate and multivariable analyses. All HPV types will be considered individually in the tables presenting descriptive statistics by HPV type as well as high risk and low risk categories. The high risk (oncogenic) category is obtained by grouping together HPV types 16, 18, 31, 33, 35, 39, 45, 51, 52, 56, 58, 59, 66, and 68. The low risk (non-oncogenic) category is obtained by grouping together HPV types 6, 11, 34, 40, 42, 43, 44, 53, 54, 70 and 74. In some cases, the category “No cervical HPV infection” will be added in the categorization for univariate and multivariable analyses.

- HPV infection category: 6-month persistent, less than 6-month persistent, transient, last visit detected.
- Previous cervical HPV infection: No; Yes, with at least one high risk HPV type; Yes, with only low risk HPV type.
- Histopathologically-confirmed CIN2+ (or CIN1+, or CIN3+) following the reference cervical HPV infection, associated with a different HPV type, and preceding the CIN2+ (or CIN1+, or CIN3+) associated with the same HPV type as the reference infection (i.e. date of CIN2+ (or CIN1+, or CIN3+) following the reference infection strictly inferior to date of CIN2+ (or CIN1+, or CIN3+) associated with the same HPV type as the reference infection): No; Yes, with at least one high risk HPV type; Yes, with only low risk HPV type.

- Histopathologically-confirmed CIN2+ (or CIN1+, or CIN3+) preceding the reference cervical HPV infection, associated with a different HPV type : No; Yes, with at least one high risk HPV type; Yes, with only low risk HPV type.
- Co-infection with other HPV types (concomitant cervical HPV infections): No; Yes, with at least one high risk HPV type; Yes, with only low risk HPV type.

Co-infection with other HPV types is defined as the detection of these HPV types at time of the onset of the reference cervical HPV infection or, if this infection is persistent, during the duration of the reference cervical HPV infection until its end or until the occurrence of the event, whichever comes first.

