#### 6.2.4.5 Statistical methods

The time between persistent cervical HPV infections and lesions will be analyzed using Kaplan-Meier method and Cox regression models.

Kaplan-Meier curves presenting the cumulative probability of lesions following 6-month persistent cervical HPV infections will be displayed and compared between groups for determinants of interest using the Log-rank test (univariate analyses). Cox regression models will be also performed for the univariate analyses in order to obtain unadjusted hazards ratios of the determinants of interest.

In addition, a multivariable Cox regression model will be performed in order to estimate the relative contribution of each determinant adjusting for the simultaneous effects of the other covariates. The model will include: time-independent covariates (e.g., age and region at study entry), time-independent covariates re-assessed at follow-up visits (e.g., behavioral determinants updated over the follow-up period using the yearly behavioral questionnaires) and time-dependent covariates (e.g., concomitant cervical HPV infections, i.e. co-infection). Also, some of the determinants will be distinguished depending on whether they started

before or after the 6-month persistent cervical HPV infections leading to the lesions in order to differentiate their effects in the pathway leading from cervical HPV infection to lesion (cf. Sections 4.4.2 and 4.4.3 for the definition of behavioral and clinical determinants and Section 8.5.1 for the list of determinants that will be taken into account in the analysis).

As the same subject may contribute to more than one observation (e.g., the same women may have several persistent cervical HPV infections of same or different HPV types leading or not to lesions associated with these HPV types), the analysis will be performed using an appropriate approach (counting process, clustering etc.) carried out either by a standard or a stratified Cox model depending on whether i) the recurrent events may be considered as identical or different and ii) the assumption that the estimated proportional hazards are constant over time is fulfilled or not [Andersen et al., 1993; Prentice et al, 1981; Kelly and Lim, 2000; Kleinbaum and Klein, 2005].

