As the different events from a same subject are treated as independent observations in the Cox model, robust variance estimates adjusted for the correlation within subjects will be obtained using the robust estimation method derived as an extension of the information sandwich estimator [Lin and Wei, 1989; Zeger and Liang, 1986].

The choice of the best fitted model will be based on the Akaike's Information Criterion (AIC) and the Schwarz Bayesian Criterion (SBC) but also on the consistency of the effects of the covariates observed in the different multivariable models.

Results from the multivariable time survival analyses (Cox model) will include mean and median (if estimable) time (with 95% CI) and hazards ratios (with 95% CI). The survival curves predicted by the model will be displayed.

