|                     | Histopathologically-confirmed CIN1+ preceding the reference cervical HPV infection, associated with a different HPV type                                                                                                                   | Class  | No
Yes, with at least one high risk HPV type
Yes, with only low risk HPV type    | No             | Re-assessed at each visit |
|                     | Co-infection* with other HPV types (concomitant cervical HPV infection)                                                                                                                                                                    | Class  | No
Yes, with at least one high risk HPV type
Yes, with only low risk HPV type    | Yes            | Re-assessed at each visit |

\$ Only for the analysis of time between any cervical HPV infections and lesions.

\* Co-infection with other HPV types is defined as the detection of these HPV types at time of the onset of the reference cervical HPV infection or, if this infection is persistent, during the duration of the reference cervical HPV infection until its end or until the occurrence of the event, whichever comes first.

Consequently any cervical HPV infection which onset is prior to the onset of the reference cervical HPV infection will be considered as a previous cervical HPV infection and any cervical infection which onset if after the end of the reference cervical HPV infection and before the occurrence of the event will not be considered as a co-infection.

However, when analyzed as time-varying covariables, co-infections will be considered until the occurrence of the event (e.g., lesion).

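### Adjusted survival curves and mean/median times to CIN are to be predicted from a Cox model with two internal time-dependent covariates and no stated covariate path

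*SAP*

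**What the plan says.** Section 6.2.4.5 lists what the multivariable Cox model will contain: fixed covariates, covariates re-assessed at visits, and "time-dependent covariates (e.g., concomitant cervical HPV infections, i.e. co-infection". Table 9.5.1 marks two covariates as time-dependent. One is co-infection with other HPV types. The other is CIN of a different HPV type that follows the reference infection and precedes the event.

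The same section then sets the outputs: "Results from the multivariable time survival analyses (Cox model) will include mean and median (if estimable) time (with 95% CI", together with hazard ratios. It adds: "The survival curves predicted by the model will be displayed".

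No covariate values or path are given for these predictions, and no reduced model, landmark or multistate method is named. Model choice rests on AIC, SBC and consistency of effects ("The choice of the best fitted model will be based on the Akaike's Information Criterion (AIC"), and nothing there removes the time-dependent covariates before prediction. Section 6.2.5.5 applies the same methods to the time from any infection to lesion. Both analyses cover CIN1+, CIN2+ and CIN3+, so six outcomes are involved, including the primary one.

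**The concern.** With covariates fixed at time zero, a Cox model turns a hazard into a survival curve directly. With a time-dependent covariate, the curve also needs the covariate's value at every later time. If the covariate is internal, meaning it arises from the woman's own course and is followed only until the event, the usual link between cumulative hazard and survival no longer yields a survival probability.

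Both covariates here are internal. For co-infection, table 9.5.1 says: "However, when analyzed as time-varying covariables, co-infections will be considered until the occurrence of the event (e.g., lesion". Different-type following CIN is tied to the event date in 4.4.2: it must be "strictly inferior to date of CIN2+ (or CIN1+, or CIN3+) associated with the same HPV type as the reference infection".

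At stake are the adjusted curves and adjusted mean/median times for the six lesion outcomes. A reader would take them as the time course for infections of a given kind, and they would not be that.

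**Working it through.** **Nothing to reproduce.** The SAP gives no event rate, switching rate or hazard ratio for this analysis. The argument is therefore checked by logic first, and its size under stated assumptions.

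**Logic.** By definition, following CIN occurs after the reference infection, so every infection starts at No and may switch to Yes. A constant path can then be read three ways:
- Yes throughout: no infection has this path.
- No throughout: membership depends on the future, so the group cannot be identified at onset.
- The mean value: no infection has it.

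Co-infection may already be Yes at onset, but its later path is equally unknown.

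**Size: model.** Assume a constant event hazard h0 while the covariate is No, switching from No to Yes at rate λ, and hazard h0 × HR after the switch. Let t = 48 months, the planned follow-up in SAP 3.1, and a = h0 + λ.
- Predicted risk at a fixed value z: 1 − exp(−h0 × t × HR^z).
- True survival of infections starting at No: S(t) = exp(−a t) + λ × [exp(−h0 HR t) − exp(−a t)] / (a − h0 HR).
- Survival among infections never observed to switch: exp(−a t) / {(h0/a) × [1 − exp(−a t)] + exp(−a t)}.

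**One case** (assumed: base risk 10%, 50% switching by 48 months, HR 3):
- h0 = −ln(0.90)/48 = 0.00220; λ = ln(2)/48 = 0.01444; a = 0.01664; h0 × HR = 0.00659.
- Held at No: 1 − 0.90 = 10.0%.
- Held at Yes: 1 − 0.90^3 = 27.1%.
- Held at the person-time mean (0.26): 1 − 0.90^(3^0.26) = 13.1%.
- True: S = 0.450 + 1.437 × (0.729 − 0.450) = 0.851, so the risk is 14.9% (simulation of 200,000 infections: 15.0%).
- Never observed to switch: 0.450 / (0.132 × 0.550 + 0.450) = 0.861, so the risk is 13.9% (simulation 14.0%). The curve held at No, at 10.0%, does not describe this group either.

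**Range.** Base risk was 5, 10 or 20%, switching 20 or 50%, and HR 0.5, 2 or 3. Selected 48-month risks:

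| Base risk | Switching | HR | Held at No | Held at mean | True |
|---|---|---|---|---|---|
| 5% | 20% | 0.5 | 5.0% | 4.7% | 4.7% |
| 5% | 50% | 3 | 5.0% | 6.7% | 7.6% |
| 10% | 50% | 3 | 10.0% | 13.1% | 14.9% |
| 20% | 50% | 0.5 | 20.0% | 16.8% | 17.4% |
| 20% | 50% | 3 | 20.0% | 25.2% | 28.6% |

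Over the whole grid, the curve held at No misses by 0.3 points (5.0 against 4.7) to 8.6 points (20.0 against 28.6). The curve at the mean misses by about 0 to 3.4 points (25.2 against 28.6).

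**Medians.** The shortest implied median in the grid is ln(2)/(h0 × HR) at 20% base risk and HR 3, held at Yes, which is about 50 months. All exceed 48 months.

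**The case against.** The strongest reply is that little depends on these curves. Section 6.2.4.5 plans Kaplan-Meier curves of the cumulative probability of lesions by determinant, and 6.2.3.1 adds event densities. Neither comes from the Cox model. This stands: a reader might infer that the descriptive half of the primary objective is lost, and the SAP does not support that. What remains affected is the adjusted output, which the SAP promises separately.

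Other stronger readings also fail:
- *That a Yes-from-day-0 curve is planned.* The SAP does not say by which covariate curves will be shown. Table 9.5.1 names HPV type, a fixed covariate, as the main variable of interest, so curves by HPV type are the likelier display. The question is then where the two time-dependent covariates are held, which is why the No and mean columns above measure the size and the 27.1% does not.
- *That Yes on day 0 is impossible for both covariates.* It is impossible only for following CIN. Section 4.4.2 allows co-infection at onset.
- *That reported medians would be wrong.* They are promised only if estimable, and under the assumed rates none is reached within 48 months. That condition does not protect the curves, nor any mean computed from them.
- *That the hazard ratios are compromised.* This prediction problem does not touch them.
- *That section 6.2.7 has the same fault.* Tables 9.5.3 and 9.5.4 mark every covariate as not time-dependent.

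It is also fair to say that a curve can be computed along a stated path with counting-process data. Such a curve is a hypothetical that treats the covariate as external. The SAP states neither a path nor that assumption.

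**Conclusion.** The point holds for the model-predicted curves and mean/median times in 6.2.4.5 and 6.2.5.5. As written, the plan takes them from a model with two internal time-dependent covariates, and constant or mean values of those covariates give curves that belong to no actual group of infections. The unit is the infection, so the statement concerns infections and not women.

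The size cannot be fixed from the SAP. It runs from negligible to several percentage points at 48 months and grows with base risk, switching and distance of the hazard ratio from 1. The figures rest on constant hazards, a single switching covariate and 48 months from infection onset, which is the longest follow-up possible. This is worth correcting before the adjusted curves are published. It does not threaten the hazard ratios or the Kaplan-Meier results.

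**What to change.** In 6.2.4.5, and through it 6.2.5.5, state that the model with time-dependent covariates is used for hazard ratios only. Take the adjusted curves and mean/median times for CIN1+, CIN2+ and CIN3+ from a companion Cox model whose covariates are fixed at infection onset: HPV type, region, age, co-infection at onset, and the other determinants at their onset values. Section 4.4.3 already defines the behavioral ones from the last questionnaire or visit before the infection. In the any-infection analysis, leave out infection category, because it is known only from later samples. Average the predictions over the observed covariate distribution, and state this in the SAP.

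Landmark or multistate prediction would also answer the point, with more work. Keeping the present model with a stated path, labelled as hypothetical, is the minimum.

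The cost is SAP wording and one extra model per endpoint, six in all. Section 7 records that the primary-endpoint analysis was delivered in August 2011, so any predicted curves in that delivery may have to be re-issued.

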## **6.2.5 Analysis of time between any cervical HPV infections and lesions**

### **6.2.5.1 Population**

The population for the analysis of time between any cervical HPV infections and histopathologically-confirmed CIN2+ (or CIN1+, or CIN3+) associated with the same HPV type will be restricted to subjects from the TVC-1-Control arm cohort for whom at least one cervical HPV infection (any cervical HPV infection) was detected so that a starting date is available for the computation of the time between infections and lesions.

Subjects with positive or missing HPV DNA at Month 0 for the HPV type associated with the endpoint will be taken into account in the analysis as well as subjects for whom a histopathologically-confirmed CIN2+ (or CIN1+, or CIN3+) associated with a given HPV type is detected prior to any cervical infection of that HPV type.

The cervical HPV infections of subjects positive for HPV DNA at Month 0 and negative for HPV DNA at Month 6 (for the HPV type associated with the endpoint) will be considered as transient cervical HPV infections. This is done so that these infections can be taken into account in the analyses. As a matter of fact, such cervical HPV infections may be either transient or persistent but the start date of infections which started before study entry is unknown.

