#### 4.3.1 Cervical HPV infections

- **Incident cervical HPV infection:** an incident cervical infection with a given HPV type is defined as the new detection of this HPV type (by PCR) at any time point during the follow-up period (i.e. after enrolment in the control arm of study HPV-008).
- **Transient cervical HPV infection:** a transient cervical infection with a given HPV type is defined as the detection of this HPV type (by PCR) at any single time point during the follow-up period followed by a negative sample for that HPV type at the evaluation performed 6 months after the evaluation when the cervical HPV infection was first detected.
- **6-month persistent cervical HPV infection:** a persistent cervical HPV infection (6-month definition) is defined as the detection of the same HPV type (by PCR) in cervical samples at two consecutive evaluations over approximately a 6-month interval. Thus, the algorithmic definition of a 6-month persistent infection is that there exists a sequence of positive samples with the same HPV type, not interrupted by negative samples, such that the total range is more than 5 months ( $> 150$  days). The start of the persistent cervical HPV infection is defined as the date of the first positive sample in the sequence.
- **12-month persistent cervical HPV infection:** a persistent cervical HPV infection (12-month definition) is defined as the detection of the same HPV type (by PCR) at all available time points over approximately a 12-month interval. Thus, the algorithmic definition of a 12-month persistent cervical infection is that there exists a sequence of positive samples with the same HPV type, not interrupted by negative samples, such that the total range is more than 10 months ( $> 300$  days). The start of the persistent cervical HPV infection is defined as the date of the first positive sample in the sequence.
- **Other cervical HPV infection:** other cervical HPV infections than those described above will be considered in the analysis. These infections are cervical HPV infections with duration less than 150 days and cervical HPV infections detected at the last visit and for which it is not possible to determine if they are transient or persistent.

- **Clearance of cervical HPV infection:** two definitions will be used:

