## **6.2.4 Analysis of time between persistent cervical HPV infections and lesions**

### **6.2.4.1 Population**

The population for the analysis of time between confirmed persistent cervical HPV infections (6-month definition) and histopathologically-confirmed CIN2+ (or CIN1+, or CIN3+) associated with the same HPV type will be restricted to subjects from the TVC-1-Control arm cohort for whom at least one 6-month persistent cervical HPV infection was detected so that a starting date is available for the computation of the time between persistent infections and lesions.

Subjects with positive or missing HPV DNA at Month 0 for the HPV type associated with the endpoint will be taken into account in the analysis as well as subjects for whom a histopathologically-confirmed CIN2+ (or CIN1+, or CIN3+) associated with a given HPV type is detected prior to the detection of the first 6-month persistent cervical infection of that HPV type (see Sections 6.2.4.3 and 6.2.4.4 for handling this particular case).

The cervical HPV infections of subjects positive for HPV DNA at Month 0 and negative for HPV DNA at Month 6 (for the HPV type associated with the endpoint) will be considered as transient cervical HPV infections. As a matter of fact, such cervical HPV infections may be either transient or persistent but the start date of infections which started before study entry is unknown. Consequently, these infections will not be taken into account in the analyses.

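### In the any-infection analyses, infections positive at Month 0 and negative at Month 6 are coded transient although their duration is unknown, which contaminates that covariate level to an unquantified extent

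*SAP*

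**What the plan says.** Section 4.3.1 defines a transient infection as "the detection of this HPV type (by PCR) at any single time point during the follow-up period followed by a negative sample" six months later. Under the neighbouring definition of an incident infection, the follow-up period is explained as "i.e. after enrolment in the control arm of study HPV-008".

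Section 6.2.5.1 (any-infection analyses) counts infections positive at Month 0 and negative at Month 6 for the type in question as transient, and explains: "This is done so that these infections can be taken into account in the analyses". It then adds that "such cervical HPV infections may be either transient or persistent but the start date of infections which started before study entry is unknown".

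Section 6.2.4.1 (persistent-infection analyses, including the primary one) applies the same label and makes the same concession, but ends: "Consequently, these infections will not be taken into account in the analyses". Month 0 positives as such are not barred there: "Subjects with positive or missing HPV DNA at Month 0 for the HPV type associated with the endpoint will be taken into account".

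In the any-infection analyses the label is used twice:

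- It sets the level of the covariate *HPV infection category* (4.4.2). The footnote in 9.5.1 limits this covariate to the any-infection models.
- It sets the rank in 6.2.5.3 by which a lesion is assigned to one of several same-type infections: 6-month persistent, then persistent under 150 days, then transient, then other.

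The SAP has no level for infections already present at Month 0, no planned run without these infections, and no count of them.

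**The concern.** The label in 6.2.5.1 serves to bring these infections into the analysis; the SAP does not claim to know that they were short. Once applied, however, the models treat it as a classification. An infection that lasted well over a year and ended soon after enrolment is coded like one that appeared and disappeared between neighbouring visits.

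At stake is the comparison of lesion risk between persistent and transient infections in the any-infection models for CIN1+, CIN2+ and CIN3+. If longer infections carry more lesion risk, as the order of the attribution ranking suggests the SAP itself supposes, then placing some of them in the transient level would be expected to pull the two levels together.

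**Working it through.** **What needs no assumption.** Section 3.2 schedules PCR at Months 0, 6, 12, 18, 24, 30, 36 and 48. With all visits attended, a single positive at Months 6 to 30 has a negative about 6 months before and another about 6 months after, so the infection cannot have lasted much more than 12 months. A single positive at Month 36 is followed by a 12-month gap, so the limit there is about 18 months. A Month 0 positive has no earlier sample, so there is no limit on its prior duration.

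**What needs assumptions.** The SAP states no figure on this point, so there is nothing to reproduce. For illustration, assume constant incidence and exponential infection duration with mean *m* months. These inputs are not in the SAP. Let *q* = 1 − exp(−6/*m*).

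- Share of the Month 0 positive, Month 6 negative infections already present 6 months before Month 0: *L* = exp(−6/*m*).
- Share of the transient level made up of Month 0 infections: *s* = 1 / [1 + 5*q* + (1 − exp(−12/*m*))]. The term 5*q* covers single positives at Months 6 to 30, and the last term those at Month 36.
- Share of the transient level that is both from Month 0 and long in this sense: *s* × *L*.

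For *m* = 12: *q* = 0.393, *s* = 1/(1 + 1.967 + 0.632) = 0.278, *L* = 0.607, *s* × *L* = 0.169.

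| *m* (months) | *L* | *s* | *s* × *L* |
|---|---|---|---|
| 4 | 0.223 | 0.171 | 0.038 |
| 6 | 0.368 | 0.199 | 0.073 |
| 12 | 0.607 | 0.278 | 0.169 |
| 18 | 0.717 | 0.344 | 0.247 |
| 24 | 0.779 | 0.400 | 0.312 |

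Constant past incidence is doubtful in women aged 15 to 25. If Month 0 prevalence is a fraction *k* of its steady-state value, *s* becomes *k* / [*k* + 5*q* + (1 − exp(−12/*m*))]. For *k* = 0.25 and *m* = 6, *s* = 0.058 and *s* × *L* = 0.022. For *k* = 0.5 and *m* = 18, *s* = 0.208 and *s* × *L* = 0.149. The overall range is thus about 2% to 31%. Leaving Month 36 single positives out of the level raises the top of the range to 37%.

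**Total duration over 12 months.** For the Month 0 group the share is (6/*m*) exp(−12/*m*) / *q*, which is 0.21 for *m* = 6 and 0.47 for *m* = 12. In simulation on the SAP's visits, the share among incident single positives was 2% and 4%, all of it from Month 36. Simulated mean total durations were 8.5 against 5.4 months (*m* = 6) and 14.8 against 6.1 months (*m* = 12).

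**The case against.** Several points against the concern stand in whole or in part.

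- **The transient level is not filled with long infections.** A reader might infer that it is. The SAP gives no counts, and long Month 0 infections are a minority of the level in every scenario run.
- **Transient is an observed sampling pattern, not a true duration.** Against a 150-day threshold the difference is small. In the same model, with Month 36 included, the share of the level truly lasting over 150 days is 53%, 62% and 65% without the Month 0 group, and 56%, 68% and 73% with it (*m* = 6, 12, 18). The argument rests on the long tail beyond 12 months.
- **Sections 6.2.4.1 and 6.2.5.1 do not conflict over the label.** A reader might infer that the primary analysis rejects a classification that the secondary analyses accept. Both sections use the same label. One positive followed by a negative cannot meet the observed 6-month persistence definition, so omission from 6.2.4 follows from that population's entry rule. What remains is that 6.2.4.1 gives the unknown start as its reason for omission, while 6.2.5.1 states the same fact and includes.
- **The conflict with 4.3.1 is modest.** The explanation of follow-up as post-enrolment is attached to the incident definition and is not repeated for transient infections. Section 4.2 openly admits Month 0 positives to some analyses.
- **No loss of contrast was modelled.** The check concerns durations, not lesion hazards. These women had normal or low-grade cytology at Month 0 and were PCR-negative by Month 6, so their lesion risk need not match that of other long infections. HPV type, not infection category, is the main variable of interest.
- **The ranking matters only for repeat infections.** It applies when one woman has several same-type infections separated by clearance.
- **The SAP allows changes.** Sections 6.1.2 and 6.2.8 permit documented changes to categories and complementary analyses, but neither commits to this one.

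**Conclusion.** The point holds in limited form. The any-infection analyses put infections of unknown and unbounded prior duration in the same covariate level as infections whose duration is bounded by the visit schedule, and the SAP acknowledges the uncertainty without handling it. The direction is clear: the added infections are longer on average. The extent is not. The figure of about 2% to 31% of the transient level rests on assumed durations and prevalence and is only an illustration.

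Some blurring of the persistent-versus-transient contrast is to be expected in the three any-infection secondary endpoints, provided that longer infections carry more lesion risk. Its size is not established.

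The primary analysis and the other analyses in 6.2.4 are untouched, because these infections are omitted there and the covariate is not used. A separate level also does not cure the unknown onset itself: persistent infections first seen at Month 0 share that problem.

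**What to change.** - In 4.4.2 and 9.5.1, add a level to *HPV infection category*: present at Month 0, negative at Month 6, duration unknown.
- In 6.2.5.3 and the tables of 6.2.5.4, state where this level stands in the lesion-attribution ranking.
- Report how many infections fall in it, so that the extent can be judged from data.
- Add a sensitivity run of the any-infection models without these infections, or restricted to infections with a preceding negative sample.
- Align the wording of 4.3.1, 6.2.4.1 and 6.2.5.1 on whether a Month 0 detection can count as transient, and why it is included or omitted.

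The cost is one extra covariate level and one extra model run per endpoint. It needs no new data, and the main analysis discards none.
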